### Study outcomes

The primary outcome is change in home SBP comparing the intervention and standard of care groups. The major secondary outcomes are rate of SBP change, change in diastolic blood pressure, proportion of participants achieving guideline-defined target blood pressure, patient-reported adverse effects, quality of life, proportion of participants reporting treatment withdrawal and adherence. In addition, HYPERMARKER will demonstrate methods for direct patient involvement and empowerment, as well as healthcare pathways and health economic evaluation to underpin future implementation (online supplemental table 2) for full list of trial outcomes).

### Sample size

The sample size of 400 patients using home SBP provides 99% power to detect a 1.5 mm Hg difference in SBP between the pharmacometabolomic approach and standard of care groups. Sample size calculations are based on the expected minimum of 12 baseline SBP measurements and 48 follow-up measurements by the end of the first phase and assume a 2-sided alpha of 0.05, baseline SBP of 145 mm Hg (SD 20), with a correlation between SBP measurements of 0.7.^30^ Power is retained at >85% for a 2.5 mm Hg difference in home SBP even if only 3 baseline and 12 follow-up measurements are recorded (with correlation 0.5- and 2-sided alpha 0.05).

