## Abstract

**Introduction:**

Blood pressure treatment response is variable in individual patients, and the choice of medical therapy is often dependent on clinician experience. Treatment choices could be personalised by patient empowerment and metabolomic profiles, and augmented by machine learning, but robust evaluation is lacking on how these can be combined to enhance clinical effectiveness. The HYPERMARKER trial will evaluate how an individualised choice of medication class can address the avoidable global health and economic burdens of hypertension.

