### Randomisation and allocation

Following written consent, participants will be randomised in a 1:1 ratio to either the initial standard of care (Group A) or initial use of the pharmacometabolomic approach for treatment selection (Group B). Randomisation will be stratified by site (four sites), participant age (18–69 and ≥70 years) and baseline office SBP (140–159 mm Hg or ≥160 mm Hg). As an open-label trial, both the investigator and participant will be aware of the allocation after randomisation. The pharmacometabolomic approach will be updated as additional data are obtained during the trial. Participants will have their medication class re-reviewed, with the updated pharmacometabolomic output provided to investigators for all participants, regardless of original randomised group, to ensure equity (figure 2).

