**Figure 3 F3:**
[figure not shown]
Span of individual patient factors related to metabolomics.

Machine learning can identify key variables from large, diverse biomedical and clinical datasets to generate highly accurate predictive models that can be validated across populations.^49 50^ It offers a potential pathway to personalised therapy and has already been applied to predict antihypertensive treatment response using standard clinical factors.^51^,^53^ However, large-scale studies that integrate metabolomic profiles into these models are lacking. Moreover, such models have not yet been tested in clinical trials, limiting their potential for clinical implementation.^54^

Digital tools for personalised therapeutics can significantly improve compliance and empower patients to take an active role in their healthcare decisions.^55 56^ A combined trial intervention including patient self-management and monitoring, with tailored titration, lifestyle advice and behavioural support, resulted in a mean difference in SBP of −3.4 mm Hg (95% CI −6.1 to −0.8 mm Hg) compared with usual care after 1 year (n=622).^57^ In an open‐label trial using daily home self‐monitoring with a linked smartphone app, personalised dosing of amlodipine achieved an SBP reduction of 11 mm Hg (95% CI 10 to 12, p<0.001, n=205) over 14 weeks, with high patient-reported adherence (94%).^58^ However, an individual patient data meta-analysis of randomised trials found that self-monitoring alone does not improve BP but requires a co-intervention.^59^

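### The 99% power for 1.5 mm Hg assumes no between-patient variation in true SBP change, although the trial is built on variable response; power should be shown over a range

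*Protocol article*

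**What the plan says.** All references are to the protocol article.

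- **Sample size.** "The sample size of 400 patients using home SBP provides 99% power to detect a 1.5 mm Hg difference in SBP" between the two groups. The calculation rests on at least 12 baseline and 48 follow-up readings per patient, and the authors "assume a 2-sided alpha of 0.05, baseline SBP of 145 mm Hg (SD 20), with a correlation between SBP measurements of 0.7". No other variance or correlation is given.
- **Sample size, fewer readings.** "Power is retained at >85% for a 2.5 mm Hg difference in home SBP" with only 3 baseline and 12 follow-up readings and a correlation of 0.5.
- **Randomisation and allocation.** "participants will be randomised in a 1:1 ratio", so 200 per arm.
- **Study procedures.** The baseline readings come before the medication change and the follow-up readings in the 4 weeks after it.
- **Abstract, Introduction.** "Blood pressure treatment response is variable in individual patients". The section Potential for personalised medicine adds that a repeated cross-over trial found substantial differences in response, with a modelled gain of 4.4 mm Hg from choosing each patient's best treatment.
- **Discussion.** As background, an open-label home-monitoring trial with an "SBP reduction of 11 mm Hg (95% CI 10 to 12, p<0.001, n=205") over 14 weeks.

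**The concern.** Treatment changes between the baseline and follow-up readings. If patients respond differently, two readings from the same period are more alike than two readings from different periods, so the across-period correlation is lower than the within-period one. Using 0.7 for both leaves out the spread of true change between patients. Averaging 12 and 48 readings removes reading error but leaves that spread untouched, so the number of readings cannot by itself deliver 99%.

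This matters because home SBP against standard of care is the primary objective. A reader who takes 99% at face value could treat a neutral result as nearly excluding a 1.5 mm Hg effect. Under moderate variation in response the trial could miss such an effect fairly often.

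**Working it through.** **Inputs.** n = 200 per arm; SD of one reading 20; p = 12 baseline and r = 48 follow-up readings; correlation ρ = 0.7; two-sided alpha 0.05; difference 1.5 mm Hg. All are from Sample size, except the 1:1 allocation.

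**1. Reproduce the plan's figures.** Repeated-measures ANCOVA with one common correlation:

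V = SD² × [(1 + (r−1)ρ)/r − pρ²/(1 + (p−1)ρ)]

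- *12 + 48 readings, ρ = 0.7:* V = 400 × (0.70625 − 0.67586) = 12.16. The SD is 3.49, SE = 3.49 × √(2/200) = 0.349, and power for 1.5 mm Hg is **99.0%**.
- *3 + 12 readings, ρ = 0.5:* V = 400 × (0.54167 − 0.375) = 66.7. The SD is 8.16, SE = 0.816, and power for 2.5 mm Hg is **86.5%**, which fits the stated >85%.

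A change-score formula gives 98.9% for the first scenario but only 78% for the second, so ANCOVA is the formula that fits both.

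**2. What the single correlation implies.** With one ρ for all pairs, the variance of a patient's mean change is

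SD² × (1 − ρ) × (1/12 + 1/48) = 400 × 0.3 × 0.104 = 12.5.

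This is reading noise only. The between-patient variance of true change is exactly zero.

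**3. Add a true-response SD, τ, to the article's own noise.** Use V + τ² with V = 12.16, taking response as independent of baseline, for a 1.5 mm Hg difference:

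| τ (mm Hg) | Total SD | Power |
|---|---|---|
| 0 | 3.49 | 99% |
| 2 | 4.02 | 96% |
| 3 | 4.60 | 90% |
| 4 | 5.31 | 81% |
| 5 | 6.10 | 69% |
| 6.4 | 7.29 | 54% |
| 8 | 8.73 | 40% |

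**4. The same point in terms of correlation.** Keep 0.70 within each period and lower only the across-period value, ρx. The bracket in step 1 becomes 0.70625 − ρx²/0.725.

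| ρx | V | SD | Power for 1.5 mm Hg |
|---|---|---|---|
| 0.68 | 27.4 | 5.23 | 82% |
| 0.65 | 49.4 | 7.03 | 57% |
| 0.60 | 83.9 | 9.16 | 37% |

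With equal variances in both periods, ρx = 0.68 corresponds to a true-change SD of √(2 × 400 × 0.02) = 4.0 mm Hg, in line with the row τ = 4 in step 3.

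**5. Fewer readings.** With SE 0.816 from step 1, power for the planned 1.5 mm Hg is **45%**. Power for 2.5 mm Hg also falls once response varies: at τ = 4 the SD is √(66.7 + 16) = 9.09 and power is 79%; at τ = 6.4 the SD is 10.37 and power is 67%.

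**6. One illustration from the article.** If the interval of 10 to 12 is a simple mean over 205 patients, the SD of change is (1/1.96) × √205 = 7.3 and power for 1.5 mm Hg is 54%. The limits are rounded to whole mm Hg, so the half-width could be 0.5 to 1.5. That gives an SD of 3.7 to 11.0 and power of 98% to 28%. The 7.3 is a total SD; net of the noise in step 2 it is √(7.3² − 12.5) ≈ 6.4.

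**The case against.** The strongest reply is that nothing has been miscalculated. Both published figures follow from the stated inputs, so this is a disputed assumption and not an arithmetic error. That stands, and the point is put on that footing.

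Four stronger readings are tempting, and the documents do not support them.

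- **That the true power is 54%.** A reader might infer this from the cited n=205 trial. That trial is Discussion background, not a sample-size input. It studied 14 weeks of personalised dosing of one drug, not 4 weeks after a choice of class. The SD is back-calculated from a rounded interval under an assumed simple mean, and rounding alone allows almost the stated 99% at the favourable end. It can serve only as an illustration.
- **That 99% needs every patient to respond identically.** This is too strict. A response SD of 1 mm Hg still gives about 98%, and 2 mm Hg gives 96%.
- **That the other self-monitoring trial in the Discussion (n=622), or the 80% monitoring adherence, lowers power further.** The first is a one-year comparison of a multi-component programme and is not comparable. The second is adherence to weekly measurement, not dropout, and the planned model uses all available readings.
- **That the fewer-readings sentence conceals its target.** It states 2.5 mm Hg openly. The fault is that "Power is retained at >85% for a 2.5 mm Hg difference in home SBP" follows directly on a claim for 1.5 mm Hg and invites the reader to carry it over.

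The planned covariate adjustment might also absorb some of the response variance, and a proof-of-concept result can be judged from its confidence interval. Both are fair, but neither justifies a response variance of zero.

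**Conclusion.** The concern holds as a criticism of an assumption. The 99% is right for its inputs, but those inputs exclude between-patient variation in true change, which the article gives as the reason for the trial. The conclusion needs no outside source: with the article's own noise, power for 1.5 mm Hg passes from about 96% to 40% as the true-response SD goes from 2 to 8 mm Hg, and a fall of only 0.02 in the across-period correlation brings it to about 82%. The 45% for 1.5 mm Hg in the fewer-readings scenario follows from the Sample size section alone.

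These results assume 200 analysed patients per arm, the ANCOVA formula that fits both published figures, and (in the τ calculations) response independent of baseline. The documents give no value for the response SD, so no single figure can replace the 99%.

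**What to change.** Keep 400 patients and revise the Sample size paragraph:

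1. State an explicit between-patient SD of true SBP change, with its justification, or equivalently a baseline-to-follow-up correlation below the within-period one.
2. Replace the single 99% by power over a range, such as the values for response SDs of 2 to 8 mm Hg above, and say that 99% is the limit with no variation in response.
3. If the n=205 trial is used, show it as one illustration with its rounding range (SD 3.7 to 11.0; power 98% to 28%).
4. For 3 + 12 readings and correlation 0.5, give the 45% for 1.5 mm Hg beside the >85% for 2.5 mm Hg, and note that the latter falls to about 79% at a response SD of 4 and 67% at 6.4.

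The cost is rewording and a less favourable stated power. Sample size, design and analysis stay as they are.

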### Statistical analysis

A statistical analysis plan will be drafted and agreed upon prior to database unlock. The primary analysis will follow the intention-to-treat principle, analysing all participants in their originally assigned groups regardless of compliance with the allocated group and with no imputation for any missing data. Sensitivity analyses will include ‘as-treated’ and ‘per-protocol’ analyses. The primary outcome of change in home SBP using multiple repeated measurements will be analysed using generalised linear models using a random-effects estimator and exchangeable correlation matrix. These account for all available SBP readings, accommodate variability in measurement frequency and intervals between participants and account for correlation between repeated measures. Models will include adjustment for variables used in the randomised stratification (age and site), as well as gender, prior blood pressure treatment and relevant comorbidities. Secondary outcomes will be analysed using the same methods as described above (adjusted mean difference (for continuous outcomes), logistic or log-binomial regression (for categorical outcomes), χ^2^ or Poisson regression (for count data) and incidence rate ratio (for adverse events). A p value<0.05 will be considered statistically significant.

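### The primary model's adjustment list omits baseline SBP, which is a stratification factor, and the text does not state the baseline handling that the fallback power figure requires

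*Protocol article*

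**What the plan says.** Under Randomisation and allocation, the protocol article names three stratification factors: "Randomisation will be stratified by site (four sites), participant age (18–69 and ≥70 years) and baseline office SBP (140–159 mm Hg or ≥160 mm Hg".

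Under Statistical analysis, the adjustment set is given as "Models will include adjustment for variables used in the randomised stratification (age and site), as well as gender", followed by earlier antihypertensive treatment and comorbidities. The parenthesis names two of the three factors. The primary outcome is change in home SBP, analysed from all available readings with a random-effects model and an exchangeable correlation.

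Under Sample size, the headline claim is "The sample size of 400 patients using home SBP provides 99% power to detect a 1.5 mm Hg difference in SBP", resting on an "expected minimum of 12 baseline SBP measurements and 48 follow-up measurements by the end of the first phase", SD 20, correlation 0.7 and two-sided alpha 0.05. A fallback claim follows: "Power is retained at >85% for a 2.5 mm Hg difference in home SBP", with 3 baseline and 12 follow-up readings and correlation 0.5. Allocation is equal between the arms.

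**The concern.** There are two linked but distinct problems.

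The first is a contradiction in the text. An analyst who follows the Statistical analysis section would leave out a factor on which randomisation was stratified. That factor is a baseline measure of systolic pressure, the quantity the trial sets out to change. The rest of the adjustment list does not restore it.

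The second concerns power. Both claims count baseline readings, so the calculation uses them in some way. The analysis text does not say how baseline home SBP enters the model, and the precision differs between the possible ways. The fallback scenario is the plan's own safeguard against sparse home monitoring, so it matters whether the described analysis supports that figure.

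**Working it through.** **Inputs** (Sample size; Randomisation and allocation): 400 participants at 1:1, so 200 per arm; SD 20, so variance 400; two-sided alpha 0.05. Headline: p = 12 baseline and r = 48 follow-up readings, correlation ρ = 0.7, difference 1.5 mm Hg. Fallback: p = 3, r = 12, ρ = 0.5, difference 2.5 mm Hg.

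**Formulas** (exchangeable correlation, per-participant variance):

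- Change score, follow-up mean minus baseline mean: 400 × (1 − ρ) × (1/p + 1/r).
- Baseline mean as covariate: 400 × [(1 + (r − 1)ρ)/r − pρ²/(1 + (p − 1)ρ)].
- SE of the difference = √(variance × 2/200); power = Φ(difference/SE − 1.96).

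**Reproducing the plan's figures, with baseline as covariate**

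- Headline: 400 × (33.9/48 − 12 × 0.49/8.7) = 400 × (0.70625 − 0.67586) = 12.16. SE 0.349. Power Φ(4.302 − 1.96) = 99.0%.
- Fallback: 400 × (6.5/12 − 3 × 0.25/2) = 400 × (0.54167 − 0.375) = 66.67. SE 0.8165. Power Φ(3.062 − 1.96) = 86.5%.

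Both stated figures are reproduced.

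**Change score without the covariate**

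- Headline: 400 × 0.3 × (1/12 + 1/48) = 12.5. SE 0.354. Power Φ(4.243 − 1.96) = 98.9%.
- Fallback: 400 × 0.5 × (1/3 + 1/12) = 83.33. SE 0.913. Power Φ(2.739 − 1.96) = 78.2%.

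The fallback variance ratio is 83.33/66.67 = 1.25. For 85% power in the fallback, the change score needs 480 participants in total, against 384 with the covariate.

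**Model of all readings.** Exact generalised least squares on baseline and follow-up readings together gives the change-score SE when each arm has its own baseline mean (0.354 and 0.913). It gives the covariate-adjusted SE when the arms share one baseline mean (0.349 and 0.8165). A random-effects model of all readings can therefore give either result, depending on a constraint that the text does not mention.

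**Office stratum against home baseline.** The omitted stratification factor is office SBP cut at 160 mm Hg. The power calculation uses the mean of the home readings. Under the exchangeable model, a participant's change does not depend on their underlying level, so adding the office stratum to a change-score model would recover essentially none of the lost precision. Correcting the stratification list does not repair the fallback power.

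**The case against.** The strongest reply is that the primary outcome is a change, so baseline is already used by subtraction, and the article leaves the model form open. If baseline readings enter as responses with a common baseline mean, the 86.5% is delivered as it stands. The full protocol is a supplement not shown here, and the analysis plan is still to be written. This stands to the extent that one cannot say the planned analysis fails to reach the stated power. One can say only that the text does not state the handling which the figure requires. It does not answer the contradiction over stratification: the article chose to list the factors and left one out.

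A reader might also infer more than the documents support:

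- *That the headline power depends on the covariate.* It does not: a plain change score gives 98.9%.
- *That follow-up readings will be compared with baseline ignored, with a far larger loss of power.* The outcome is defined as change and the calculation counts baseline readings, so no such analysis is planned. The variance of 83.3 is that of a change score, which does use baseline.
- *That chance baseline imbalance is left in the estimate.* A change score subtracts baseline with coefficient 1. The optimal coefficient, pρ/(1 + (p − 1)ρ), is 8.4/8.7 = 0.966 in the headline case and 1.5/2 = 0.75 in the fallback. An imbalance is therefore over-corrected, slightly in the first case and by a quarter of its size in the second.

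**Conclusion.** The concern holds in two parts. First, the article contradicts itself on the stratification factors, and its adjustment list contains no baseline SBP. This needs no assumption, and nothing in the text shown resolves it. Second, the fallback claim of more than 85% power requires baseline home SBP as a covariate or a common baseline mean (86.5%). A change-score analysis with neither falls about 8 points lower, at 78.2%. The headline claim is safe under both.

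The power figures rest on the article's own SD and correlations, an exchangeable structure, two-sided 0.05 and 200 analysed per arm with no dropout. The second part concerns what the text leaves unstated. It does not show that the final analysis will be underpowered.

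**What to change.** Make two separate changes under Statistical analysis.

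1. Replace the parenthesis so that the stratification variables read: site, age and baseline office SBP.
2. State that the participant's mean baseline home SBP enters the primary model as a continuous covariate, or that a constrained longitudinal model with a common baseline mean is used. Handle diastolic pressure the same way, with its own baseline.

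If neither option in the second change is adopted, restate the fallback power under Sample size as about 78%.

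The cost is a sentence or two in the protocol, carried into the analysis plan. Office SBP is recorded for stratification and the baseline home readings are already requested, so nothing new has to be collected.

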### Study procedures

Baseline assessments at enrolment include collection of participant demographic data, medical and medication history and patient-reported outcome questionnaires, including quality of life and food intake questionnaires and use of healthcare services in primary and secondary care. Individual metabolomic profiles are generated using a plasma sample taken at baseline and processed using a high-throughput liquid chromatography-mass spectrometry assay. Following enrolment, the trial will be conducted remotely with the provision of a home blood pressure device and smartphone application. Each participant will be asked to capture at least 1 week of home blood pressure measurements after randomisation and before changes to medications are made. A further 4 weeks of home blood pressure recordings will be requested after each medication change/review, with patient-reported quality of life, medication adherence, adverse events and healthcare consumption recorded at the end of each intervention phase via questionnaires completed using the participants' own electronic device (figure 2).

Home blood pressures will be measured using a semi-automatic, validated and Conformité Européenne (CE)-marked monitor (Rossmax Z5). Using a secure Bluetooth protocol, measurements are transferred to a mobile application (Viduet Health) on the participants' phones and then securely transferred to a joint patient, physician and researcher portal to inform medication review. Home blood pressure measurements will be taken for at least 3 days per monitoring week, with participants asked to record at least two measurements, taken in the morning and evening on each day.

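### The covariate list that secondary outcomes inherit does not name the outcome's own enrolment value, although quality of life and healthcare use are both collected at enrolment

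*Protocol article*

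**What the plan says.** All references are to the protocol article.

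- **Study procedures** lists among the baseline assessments at enrolment "patient-reported outcome questionnaires, including quality of life and food intake questionnaires and use of healthcare services in primary and secondary care". It then has "patient-reported quality of life, medication adherence, adverse events and healthcare consumption recorded at the end of each intervention phase".
- **Abstract (Methods and analysis)** names quality of life and healthcare utilisation as secondary outcomes. **Study outcomes** puts quality of life among the major secondary outcomes. There it speaks of change for systolic and diastolic pressure, but lists quality of life without that word.
- **Statistical analysis** names the covariates: age and site from the stratification, then gender, previous blood pressure treatment and relevant comorbidities. It continues: "Secondary outcomes will be analysed using the same methods as described above (adjusted mean difference (for continuous outcomes". For counts it offers a χ² test or Poisson regression. It says that a SAP will be agreed later.

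No outcome's own baseline value is named as a covariate. Nothing says that baseline values are excluded.

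**The concern.** Everyone receives the updated intervention in the second phase, so the randomised comparison of quality of life rests on one enrolment score and one score at the end of the first phase. With so few values per person, the enrolment score is usually the best single predictor of the later score. A list that goes down to gender and comorbidities but leaves this score out, if followed as written, gives a wider confidence interval than the collected data allow. It also lets a chance difference between arms at enrolment pass partly into the estimate. The same reasoning applies in kind to healthcare use, which is relevant to the economic evaluation.

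**Working it through.** **Inputs from the article.** 400 patients ("The sample size of 400 patients using home SBP provides 99% power to detect a 1.5 mm Hg difference in SBP"); "participants will be randomised in a 1:1 ratio", so 200 per arm; "assume a 2-sided alpha of 0.05". For home SBP only: "expected minimum of 12 baseline SBP measurements and 48 follow-up measurements by the end of the first phase" and "baseline SBP of 145 mm Hg (SD 20), with a correlation between SBP measurements of 0.7". The second power scenario has 3 baseline and 12 follow-up readings, correlation 0.5, a 2.5 mm Hg difference and power above 85%. The article gives no SD, correlation or target difference for quality of life or healthcare use.

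**Step 1: the plan's own power figures.** Take p baseline readings, m follow-up readings and exchangeable correlation ρ. Let A = (1 + (m − 1)ρ)/m and B = (1 + (p − 1)ρ)/p. In units of SD², the variances per person are:

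- follow-up only: A
- change score: A + B − 2ρ
- baseline-adjusted (ANCOVA): A − ρ²/B

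First scenario: A = 33.9/48 = 0.70625 and B = 8.7/12 = 0.725. The ANCOVA variance is 0.70625 − 0.49/0.725 = 0.0304, so the SD is 20 × √0.0304 = 3.49 mm Hg. The standard error of the difference is 3.49 × √(2/200) = 0.349. Power is Φ(1.5/0.349 − 1.96) = 99.0%.

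Second scenario: A = 6.5/12 = 0.5417 and B = 2/3. The ANCOVA variance is 0.5417 − 0.375 = 0.1667, SD 8.165, standard error 0.8165. Power is Φ(2.5/0.8165 − 1.96) = 86.5%.

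| Analysis | 1.5 mm Hg (stated 99%) | 2.5 mm Hg (stated >85%) |
|---|---|---|
| Follow-up only | 14.3% | 39.7% |
| Change score | 98.9% | 78.2% |
| Baseline-adjusted | 99.0% | 86.5% |

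Of these three, only baseline adjustment reproduces both figures. For SBP, the design therefore appears to rely on baseline information that the covariate list does not name.

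**Step 2: quality of life, one enrolment and one follow-up score.** Relative to a follow-up-only comparison, the variance is 1 − r² with adjustment and 2(1 − r) for a change score. The difference detectable with 80% power is (1.96 + 0.842) × √(2/200) = 0.280 SD unadjusted, and 0.280 × √(1 − r²) adjusted. Every r below is an assumption.

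| r | Adjusted variance | Variance cut | SE cut | Change-score variance | Detectable difference, adjusted (SD) |
|---|---|---|---|---|---|
| 0.2 | 0.96 | 4% | 2% | 1.60 | 0.274 |
| 0.3 | 0.91 | 9% | 5% | 1.40 | 0.267 |
| 0.4 | 0.84 | 16% | 8% | 1.20 | 0.257 |
| 0.5 | 0.75 | 25% | 13% | 1.00 | 0.243 |
| 0.6 | 0.64 | 36% | 20% | 0.80 | 0.224 |
| 0.7 | 0.51 | 49% | 29% | 0.60 | 0.200 |

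**Step 3: against a change score.** The ratio of adjusted to change-score variance is (1 − r²)/(2(1 − r)) = (1 + r)/2, which is never above 1. It is 0.75 at r = 0.5 (25% less variance) and 0.85 at r = 0.7 (15% less).

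**Step 4: allowing for the listed covariates.** Suppose they already explain a shared 10% of both scores (an assumption). The partial correlation is (r − 0.1)/0.9, which is 0.444 at r = 0.5 and 0.667 at r = 0.7. The further variance cut is 20% and 44%, instead of 25% and 49%.

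**Step 5: chance imbalance.** The standard error of the enrolment difference between arms is √(2/200) = 0.1 SD. An imbalance of that size moves a follow-up-only estimate by r × 0.1, which is 0.05–0.07 SD for r of 0.5–0.7.

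**Step 6: healthcare use.** This is probably a count, and the 1 − r² rule does not carry over directly to Poisson regression. A plain χ² test takes no covariates. No size is claimed for this outcome.

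**The case against.** The strongest objection is that an omission is not an exclusion. The list is not said to be complete, and both the full protocol and the SAP, which are not shown, could add the covariate. The words about using the same methods point to an analysis of change whose power depends on baseline readings, so the enrolment score might already enter as a covariate, a change score or a repeated measure. This stands to the extent that a reader might infer that the plan analyses these outcomes without their enrolment values, and the article does not say that. It does not remove the point. The article fixes a specific list and applies it to secondary outcomes, Study outcomes does not describe quality of life as a change, and adjustment is at least as precise as a change score (step 3).

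A reader might also infer that a quarter to a half of the available precision is thrown away. The documents do not support that as a fact. It is a share of variance, it needs r of 0.5–0.7, and the article gives those correlations for SBP readings only. On the standard-error scale the same range is 13–29%.

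Nor do these outcomes carry the trial's claim about side effects. Patient-reported adverse effects are a separate outcome, analysed by incidence rate ratio, and Study procedures lists no enrolment value for them.

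Finally, no bias is shown. The randomised comparison is valid without the covariate, and its confidence interval already allows for chance imbalance.

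**Conclusion.** The point holds as one of efficiency. The stated list, followed literally, leaves out a covariate that is already collected. For quality of life, the gain over a follow-up-only analysis ranges from small (4% of variance at r = 0.2) to large (49% at r = 0.7), depending on a correlation that the documents do not give. Those figures assume 200 analysed patients per arm, a continuous score and a linear relation. For healthcare use the direction is the same where a regression model is fitted, but the size is unknown. That the enrolment questionnaires precede allocation is also inferred: the article says only that they are taken at enrolment and that randomisation follows consent.

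**What to change.** Add to Statistical analysis, or carry into the SAP: *Quality of life will be adjusted for its own enrolment value as a continuous covariate, in addition to the covariates listed. Healthcare use, where modelled by regression rather than compared by a χ² test, will include its enrolment value as a covariate.* Confirm in Study procedures that the enrolment questionnaires are completed before allocation is known; in an open-label trial, answers given afterwards would not be safe covariates.

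The cost is a sentence or two and no new data. Because the primary analysis plans no imputation, the SAP should also say how participants without an enrolment score are handled, since they would otherwise drop out of the adjusted model. The change should be settled before outcome data are seen.
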